## Abstract

**Introduction:**

Reduced-dose schedules offer a more efficient and affordable way to use pneumococcal conjugate vaccines (PCVs). Such schedules rely primarily on the maintenance of herd protection. The Vietnam Pneumococcal Trial II (VPT-II) will evaluate reduced-dose schedules of PCV10 and PCV13 utilising an unvaccinated control group. Schedules will be compared in relation to their effect on nasopharyngeal carriage and immunogenicity.

**Methods and analysis:**

VPT-II is a single-blind open-label randomised controlled trial of 2500 infants in three districts of Ho Chi Minh City, Vietnam. Eligible infants have no clinically significant maternal or perinatal history and are born at or after 36 weeks’ gestation. Participants are recruited at 2 months of age and randomly assigned (4:4:4:4:9) using block randomisation, stratified by district, to one of five groups: four intervention groups that receive PCV10 in a 0+1 (at 12 months) or 1+1 (at 2 and 12 months) schedule or PCV13 in the same 0+1 or 1+1 schedule; and a control group (that receives a single dose of PCV10 at 24 months). Participants are followed up to 24 months of age. The primary outcome is vaccine-type pneumococcal carriage at 24 months of age. Secondary outcomes are carriage at 6, 12 and 18 months of age and the comparative immunogenicity of the different schedules in terms of antibody responses, functional antibody responses and memory B cell responses.

**Ethics and dissemination:**

Ethical approval has been obtained from the Human Research Ethics Committee of the Royal Children’s Hospital Melbourne and the Vietnam Ministry of Health Ethics Committee. The results, interpretation and conclusions will be presented to parents and guardians, at national and international conferences and published in peer-reviewed open access journals.

**Trial registration number:**

NCT03098628.

Strengths and limitations of this studyConducted in a country without routine pneumococcal conjugate vaccine (PCV) use, allowing inclusion of an unvaccinated control group and measurement of the reduction in carriage afforded by the reduced-dose schedules.Includes 0+1 and 1+1 schedules of both PCV10 and PCV13, allowing a head-to-head comparison of these two vaccines.Utilises molecular methods to provide a detailed assessment of the effect of reduced-dose schedules on pneumococcal carriage and density at key postvaccination time points.Also includes a full range of immunological outcome measures, encompassing antibody responses (by ELISA), functional antibody responses (by opsonophagocytic assay) and memory B cell responses.Does not include an accepted (WHO-recommended) schedule as an additional comparator group.

## Introduction

### Background and rationale

*Streptococcus pneumoniae* (the pneumococcus) causes significant morbidity and mortality in children under 5 years of age.^1^ There are two infant pneumococcal conjugate vaccines (PCVs) currently in use, PCV10 (*Synflorix*, GlaxoSmithKline) and PCV13 (*Prevnar-13*, Pfizer). A third PCV, *Pneumosil* (10-valent, Serum Institute of India), received WHO prequalification in December 2019. Both PCV10 and PCV13 are available through the Advanced Market Commitment mechanism, a vaccine purchase process developed by Gavi to support vaccine introduction into low-income and middle-income countries. Under this mechanism, countries pay a gradually increasing share of the cost of their Gavi-supported vaccines. Countries that have introduced PCVs with Gavi support are rapidly approaching the time when they will have to pay most, if not all, of the price of the vaccine, necessitating simpler, less expensive ways of using PCVs.

Introduction of PCV has been associated with dramatic reductions in pneumococcal disease.^2–4^ The benefits of vaccination are not only seen among vaccinated individuals (direct protection), but also in the wider unvaccinated population (indirect herd protection) through reduced nasopharyngeal (NP) carriage and transmission of vaccine type (VT) pneumococci.^5^ The manufacturers recommend a 3+1 schedule (a three-dose primary series with a booster), but WHO currently recommends a three-dose schedule (either 3+0, a three-dose primary series without a booster, or 2+1, a two-dose primary series with a booster).^6^ There is evidence to suggest that the number of doses could be further reduced with schedules designed to maintain herd protection. The UK, a country with established herd immunity from a mature PCV programme in a 2+1 schedule, recently became the first country to move to a 1+1 reduced-dose schedule. That decision was based on favourable postbooster immunogenicity compared with a 2+1 schedule, with equivalent or superior antibody levels following a 1+1 schedule for nine of the 13 serotypes in PCV13.^7^

In a 1+1 schedule, the first dose is likely to confer some protection to the recipient, and importantly provides priming for the later booster dose. A single dose of PCV7 showed 73% effectiveness against invasive pneumococcal disease (IPD) during a period of vaccine shortage in the USA,^8^ and a single dose of PCV13 in the UK showed 60% effectiveness against IPD from the additional serotypes not included in PCV7.^9^ A single dose of PCV in infancy also generates a measurable and significant immune response,^10–13^ and is better than multiple doses at priming for a booster dose for some serotypes.^7 14^ The purpose of the second dose in a 1+1 schedule is maintenance of herd protection. The timing of this dose should consider maximising individual protection of the recipient (through earlier administration) and optimising protection against carriage (through later administration); 12 months of age offers a balance between these two factors. In Vietnam, this also coincides with the first routine Japanese Encephalitis Vaccine visit. A further simplified schedule is a 0+1 schedule, involving only the second dose from a 1+1 schedule with no primary immunisation. The rationale is that a single dose will be sufficient to maintain pre-existing herd protection and control the potential re-emergence of VT, while recognising the reduced individual protection during the first year of life.

Reduced-dose (0+1 or 1+1) schedules could be implemented in countries with established PCV programmes, or they could be introduced as a primary course in their own right (in conjunction with a comprehensive catch-up campaign). Such simplified regimens present an opportunity to use existing PCVs more efficiently, and to make pneumococcal vaccination more affordable. The Vietnam Pneumococcal Trial II (VPT-II) will evaluate both PCV10 and PCV13 in a 0+1 schedule at 12 months of age and a 1+1 schedule at 2 and 12 months of age, in a largely PCV-naïve population utilising an unvaccinated control group, to assess their effect on NP carriage and immunogenicity during the first 2 years of life.

### Explanation for choice of comparators

PCV is not part of the routine infant vaccination programme in Vietnam. Inclusion of a control group that receives no infant doses of PCV is therefore justified. PCV13 was not licensed in Vietnam at the time the trial started, and PCV10 was available on the private market but not widely used. Control group participants receive a single dose of PCV10 at 24 months of age in order that all trial participants receive the benefit of pneumococcal vaccination, regardless of group allocation.

### Objectives

The overall objective of this trial is to fully evaluate the microbiological and immunological effects of 0+1 and 1+1 schedules for both PCV10 and PCV13.

#### Coprimary objectives

To evaluate the effect of a 1+1 PCV schedule on NP carriage during the first 2 years of life, comparing (A) PCV10-vaccinated and (B) PCV13-vaccinated participants with unvaccinated controlsTo evaluate the effect of a 0+1 PCV schedule on NP carriage during the first 2 years of life, comparing (A) PCV10-vaccinated and (B) PCV13-vaccinated participants with unvaccinated controls

#### Secondary objectives

To evaluate the immunogenicity of a 1+1 schedule of PCV10 or PCV13.To evaluate the immunogenicity of a 0+1 schedule of PCV10 or PCV13.To determine whether the response to a dose of PCV10 or PCV13 at 12 months of age is enhanced by a dose at 2 months of age (ie, 0+1 vs 1+1).To investigate the kinetics of the immune response to PCV vaccination at 12 months of age, comparing antibody levels and memory B cell responses 7 days and 28 days postvaccination.To examine the serotype profile of transferred maternal pneumococcal antibodies at 2 months of age.To directly compare PCV10 and PCV13 in terms of immune responses and effect on NP carriage.

### Trial design

VPT-II is a single-blind, open-label, randomised controlled phase II/III clinical trial to investigate simplified PCV schedules that are focused primarily on the generation of herd immunity. Participants are randomised to one of five groups: group V receives a 0+1 PCV10 schedule, group W receives a 0+1 PCV13 schedule, group X receives a 1+1 PCV10 schedule, group Y receives a 1+1 PCV13 schedule and group Z is a control group (that receives a single dose of PCV10 at 24 months of age). The trial registration data set can be found in online supplemental appendix 1.

10.1136/bmjopen-2021-056505.supp1Supplementary data

## Methods

### Study setting

The trial is conducted in three districts within Ho Chi Minh City, Vietnam (districts 4, 7 and 8). Districts are divided into communes, each of which has a health centre that provides preventive health services including EPI vaccines, along with primary healthcare services. The trial is conducted in one commune health centre in each district, with participants drawn from the surrounding communes within that district.

### Eligibility criteria

#### Inclusion criteria

In order to be eligible, subjects must meet all of the following criteria: aged between 2 months and 2 months plus 2 weeks, no significant maternal or perinatal history, born at or after 36 weeks gestation, written and signed informed consent from parent/legal guardian, lives within approximately 30 min of the commune health centre, and family anticipates living in the study area for the next 22 months.

#### Exclusion criteria

Subjects meeting any of the following criteria will not be eligible to participate: known allergy to any component of the vaccine, allergic reaction or anaphylactic reaction to any previous vaccine, known immunodeficiency disorder, known HIV-infected mother, known thrombocytopenia or coagulation disorder, administration or planned administration of any immunoglobulin or blood product since birth, severe birth defect requiring ongoing medical care, chronic or progressive disease, seizure disorder, history of severe illness, receipt of any 2 months vaccines through the EPI programme, or family plans on giving the infant *Quinvaxem* (diphtheria, tetanus, pertussis (DTP) *Haemophilus influenzae* type b, hepatitis B vaccine).

### Interventions

The interventions are PCV10 and PCV13. There are four intervention groups, which receive: PCV10 at 12 months of age (0+1 PCV10, group V), PCV13 at 12 months of age (0+1 PCV13, group W), PCV10 at 2 and 12 months of age (1+1 PCV10, group X), or PCV13 at 2 and 12 months of age (1+1 PCV13, group Y). Control group participants (group Z) receive a single dose of PCV10 at 24 months of age. PCV is administered by intramuscular injection into the anterolateral thigh in children less than 18 months old and in the deltoid muscle of the arm in children aged 18 months and over. All vaccinations are performed by Ministry of Health nurses specifically trained in infant vaccine administration. Single-dose vials of PCV10 and single-dose prefilled syringes of PCV13 are used.

#### Criteria for discontinuing or modifying allocated interventions

There is no modification of doses for participants in this study. If a participant has an allergic or anaphylactic response to vaccination, they will be withdrawn from the study. Participants may also be withdrawn voluntarily by the parent/legal guardian at any time, or by the study staff if they refuse any further study procedures or develop any of the exclusion criteria during the course of the study.

#### Strategies to improve and monitor adherence

Scheduled visit dates are noted on a health record card kept by the parent. If a participant does not attend a scheduled visit, a reminder phone call is made from the study clinic. If the participant cannot be contacted directly, their local Commune Health Centre is contacted for further follow-up by phone or by home visit.

#### Relevant concomitant care

Participants also receive four doses of *Infanrix-hexa*, which is a popular choice of DTP-containing vaccine but is only available on the private market, instead of the routine EPI vaccine *Quinvaxem*. With the exception of *Quinvaxem*, other vaccines are permitted in this study providing there are 2 weeks between the administration of other vaccines and study vaccines. Other medications are also permitted, with the exception of immunosuppressive medication and medications listed as contraindicated to the study vaccines.

### Outcomes

#### Primary outcome measure

The primary outcome measure to address each of the coprimary objectives is carriage of VT pneumococci, defined as carriage of serotypes 1, 4, 5, 6B, 7F, 9V, 14, 18C, 19F or 23F for the PCV10 groups, or carriage of serotypes 1, 3, 4, 5, 6A, 6B, 7F, 9V, 14, 18C, 19A, 19F or 23F for the PCV13 groups. The VT pneumococcal carriage prevalence (defined as the proportion of participants positive for VT pneumococcal carriage) will be determined at 24 months of age (primary endpoint), and also at 6, 12 and 18 months of age (secondary endpoints). Traditional culture methods (colonial morphology, α-haemolysis and the optochin test) and serotyping by latex agglutination/Quellung, with *lytA* PCR confirmation of nonencapsulated isolates, will be the main methods used to analyse NP swabs collected at 6 and 12 months of age. Quantitative real-time PCR (qPCR) targeting the *lytA* gene^15^ and serotyping by microarray^16^ will be the main methods used to analyse NP swabs collected at 18 and 24 months of age.

#### Secondary microbiological outcome measures

Carriage of any pneumococcal serotype at 6, 12, 18 and 24 months of age.Non-VT pneumococcal carriage at 6, 12, 18 and 24 months of age.Serotype-specific pneumococcal carriage at 6, 12, 18 and 24 months of age.Density of pneumococcal carriage (overall, VT, non-VT and serotype-specific) at 18 and 24 months of age.

#### Secondary immunological outcome measures

Serotype-specific IgG antibody concentrations for all PCV13 serotypes, measured by ELISA^17^ from all blood samples.Opsonisation indices (OI) for all PCV13 serotypes, measured by opsonophagocytic assay (OPA)^18^ for 50 participants per intervention group (groups V–Y) pre and 4 weeks post-12 months dose of PCV.Polysaccharide-specific memory B cells for serotypes 1, 5, 6A, 6B, 14, 19A and 23F, enumerated by ELISPOT^19^ for 50 participants per intervention group (groups V–Y) pre, 7 days post and 28 days post-12 months dose of PCV and at 24 months of age.

An overview of the procedures for collection, transportation and laboratory analyses of the blood and NP samples can be found in online supplemental appendix 2.

### Participant timeline

Participants are enrolled at 2 months of age and followed up to 24 months of age (table 1). Group V–Y participants provide NP swabs at 6 and 12 months of age, and all participants provide NP swabs at 18 and 24 months of age for analysis of the NP carriage outcomes. A subset of 200 participants per group will be included in the immunology substudy and provide three (groups V–Y) or one (group Z) blood sample(s) over the course of the trial for analysis of vaccine responses (table 2).

**Table 1 T1:** Schedule of enrolment, interventions and assessments

Age (months)	2 months	3 months	4 months	6 months	12 months	18 months	24 months
Enrolment							
Informed consent	✓						
Eligibility assessment	✓						
Allocation	✓						
Interventions							
PCV10	X				V, X		Z
PCV13	Y				W, Y		
Infanrix-hexa	✓	✓	✓			✓	
Assessments							
Demographics	✓						
Household characteristics	✓						
Nasopharyngeal swab				V-Y	V-Y	✓	✓
General health	✓	✓	✓	✓	✓	✓	✓

✓Indicates applies to all groups (V–Z), otherwise group(s) specified.

PCV, pneumococcal conjugate vaccine.

**Table 2 T2:** Schedule of blood samples for immunology substudy (subset of groups V–Z)

Age (months)	2 months	3 months	12 months	Post-12 months*	24 months
Subgroup a			V-Y†	V-Y	V-Y
Sample volume			7.5 mL	2 mL	3.5 mL
Assays			ELISA, B cell	ELISA	ELISA
Subgroup b	V	W-Y	V-Y	V-Y	
Sample volume	2 mL	2 mL	2 mL	7.5 mL	
Assays	ELISA	ELISA	ELISA	ELISA, B cell	
Subgroup c			V-Y	V-Y	V-Y
Sample volume			3.5 mL	7.5 mL	3.5 mL
Assays			ELISA	ELISA, B cell	ELISA
Subgroup d			V–Y	V–Y	V–Y
Sample volume			3.5 mL	3.5 mL	7.5 mL
Assays			ELISA, OPA‡	ELISA, OPA	ELISA, B cell
Subgroup Z-I					Z
Sample volume					3.5 mL
Assays					ELISA

*The post-12 months blood sample is collected at 12 months plus 7 days in subgroups a and b and at 12 months plus 28 days in subgroups c and d.

†3.5 mL sample for ELISA only in group W.

‡OPAs not performed in group W.

OPA, opsonophagocytic assay.

### Sample size

The target sample size is 2500 with an allocation ratio of 4:4:4:4:9. This allocation ratio provides the greatest power for a total sample size of 2500 and results in target group sizes of 400 for each of the four different infant vaccination schedules (groups V–Y) and 900 for the control group (group Z). Sample size calculations are based on the primary outcome of effect on VT pneumococcal carriage at 24 months of age. For each of the four vaccination schedules compared with the unvaccinated control group, the proposed sample size provides 82% power to detect a 40% reduction in the vaccinated group, with a two-sided type I error rate of 5%. The sample size calculations assume 15% VT pneumococcal carriage among controls, based on data from our previous pneumococcal vaccine trial in Ho Chi Minh City,^20^ and 10% lost to follow-up.

### Recruitment

Participants are recruited from infants born in the study communes during the enrolment period. Potential participants are identified from commune health centre birth records and are visited by commune health centre staff when they are approximately 6 weeks old. Verbal and written information about the trial is provided in Vietnamese and those interested in participating are referred to the study clinic when the infant is approximately 2 months old. At this time, written informed consent is obtained (online supplemental appendix 3), after which a study nurse/doctor examines the infant to ensure that all the eligibility criteria are met. Recruitment rates will be monitored on a monthly basis and meetings held with study staff and commune health centre staff to discuss any significant declines in recruitment rates.

### Allocation

The allocation ratio of Groups V, W, X, Y and Z is 4:4:4:4:9. The first 200 participants enrolled into each of groups V–Y, and a randomly selected 200 of the first 450 participants concurrently enrolled into group Z, will go into the immunology sub-study. These participants (with the exception of group Z) will be further randomised into one of four subgroups (a, b c or d) in an equal allocation ratio (table 2). Randomisation will be conducted by a database manager in Australia, using a computer-generated list of random numbers in a block randomisation scheme stratified by district. The group allocation, and subgroup allocation where relevant, is contained within a sealed envelope at the study clinic. Participants are assigned to a study group by a study doctor, using the next available envelope. The envelopes are prepared and sealed in the study office in Vietnam, by staff with no involvement in the recruitment process.

### Blinding

All outcome measures are laboratory based. Laboratory staff are blinded to the study group allocation. Laboratory samples are labelled with a unique ID number, which does not identify the study group. Given the different timing of the vaccination schedules in the different groups, the study nurses, vaccine administrators and participants will not be blinded to the study group allocation.

### Data collection methods

Data collected at the clinic are documented by dedicated, trained study staff using standardised forms. Blood samples and NP swabs are collected by staff specifically trained in the collection of samples from infants, and the volume of blood and swab quality are recorded. Laboratory data generated in both Vietnam and Australia are entered directly into dedicated databases in the laboratories by the laboratory staff and sent periodically to the data management team in Australia.

#### Retention

Appointments are documented on a parent-held health record card and a reminder phone call made the week before the scheduled visit. Missed visits are rebooked by phone and participants who miss a study visit will continue to be followed up for both sample collection and vaccine administration where possible. Participants receive a small payment at each visit towards transport costs.

### Data management

Data collected at the clinic are entered on-site into a secure, web-based Research Electronic Data Capture (REDCap) system.^21^ All entered data are monitored against the source documents for accuracy and completeness, and a series of data checks are performed on a regular basis to identify potential errors in the data. An audit trail of corrections and changes to the data is stored within the REDCap database. Immunology results are double-entered in a Microsoft Excel spreadsheet. NP culture results are entered in a Microsoft Access database and qPCR and microarray results are exported from SentiNET into Microsoft Excel or REDCap databases. The data collection forms and laboratory results are linked at the time of analysis.

### Statistical methods

#### Analysis of primary and secondary outcomes

The primary outcome of VT carriage will be presented as a proportion (prevalence). VT carriage prevalence in each of the vaccinated groups (PCV10-type carriage for groups V and X and PCV13-type carriage for groups W and Y) will be compared with unvaccinated controls. Prevalence ratios (ratio of prevalence in each vaccinated group to prevalence in unvaccinated controls) with 95% CIs will be calculated, and groups compared using χ^2^ tests (two-sided p values reported). The primary endpoint is 24 months of age, with secondary endpoints of 6, 12 and 18 months of age. At 6 and 12 months of age, time points at which no swabs were collected from group Z, swabs from the 0+1 groups (groups V and W combined) will form the unvaccinated comparator.

Immunological outcomes will be summarised in terms of: geometric mean concentrations (GMCs) and the proportion with protective antibody levels (≥0.35 µg/mL)^22^ with 95% CIs for serotype-specific IgG data, geometric mean OIs (GMOIs) and the proportion with an OI ≥8^23^ with 95% CIs for OPA data, and the mean number of antibody secreting cells per 10^6^ PBMCs for polysaccharide-specific memory B cell data. GMC and GMOI ratios and risk differences with 95% CIs will also be calculated. Means will be compared using t-tests and proportions compared using Fisher’s exact tests.

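### The stated primary comparison is a crude prevalence ratio with a chi-square test that leaves out district, the randomisation stratum, and the enrolment data; it is valid, but may give up a little precision

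*Protocol article*

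**What the plan says.** The statistical methods section of the protocol article (Analysis of primary and secondary outcomes) gives the effect measure, "Prevalence ratios (ratio of prevalence in each vaccinated group to prevalence in unvaccinated controls) with 95% CIs will be calculated", and the test, "groups compared using χ^2^ tests (two-sided p values reported"). No stratum or covariate is named.

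The Allocation section describes a "block randomisation scheme stratified by district"; there are three districts.

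Table 1 (Participant timeline) lists "Demographics" and "Household characteristics" at the 2-month enrolment visit. Both carry the tick mark, whose footnote reads "Indicates applies to all groups (V–Z), otherwise group(s) specified". No swab is taken at enrolment: "Group V–Y participants provide NP swabs at 6 and 12 months of age, and all participants provide NP swabs at 18 and 24 months". Baseline carriage therefore cannot serve as a covariate.

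The Sample size section claims 82% power per comparison for a 40% reduction from 15% control prevalence, two-sided 5%, with 400 v 900 children and 10% loss.

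**The concern.** Two kinds of baseline information exist at no extra cost, and the stated primary method uses neither.

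The first is district. Stratified randomisation balances the groups within district. If carriage differs between districts, that balance removes between-district variation from the true sampling error of the comparison. A crude chi-square does not know this, so its standard error is slightly too large. The usual advice is to analyse by the factors used to stratify.

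The second is the enrolment data on demographics and household. These are recorded at the enrolment visit and are the only other individual-level baseline data that the article shows. Some may predict carriage, but the article neither lists the variables nor says so.

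At stake is a modest amount of precision in each of the four coprimary comparisons, whose planned power is not far above 80%.

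**Working it through.** **Inputs from the Sample size section.** Control prevalence p₁ = 0.15. A 40% reduction gives p₂ = 0.15 × 0.6 = 0.09. After 10% loss, n₁ = 900 × 0.9 = 810 and n₂ = 400 × 0.9 = 360, so 1170 evaluable children per comparison. Two-sided 5%, z = 1.96.

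**Input not in the document.** R², the share of variance in 24-month carriage explained by the baseline variables. It is assumed to lie between 0 and 0.10.

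**Step 1: reproduce the stated power.**
- Pooled prevalence: (810 × 0.15 + 360 × 0.09) / 1170 = 153.9 / 1170 = 0.1315.
- Standard error under the null: √[0.1315 × 0.8685 × (1/810 + 1/360)] = 0.02141.
- Standard error under the alternative: √[0.15 × 0.85/810 + 0.09 × 0.91/360] = 0.01962.
- Power = Φ[(0.06 − 1.96 × 0.02141) / 0.01962] = Φ(0.919) = 82.1%.

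This matches the stated 82%, so the sample size was evidently built on the crude test.

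**Step 2: effect of adjustment.** The usual approximation for a standardised marginal contrast multiplies both standard errors by f = √(1 − R²). For R² = 0.05, f = 0.9747, and power = Φ[(0.06 − 1.96 × 0.02141 × 0.9747) / (0.01962 × 0.9747)] = Φ(0.999) = 84.1%. The equivalent number of extra children is 1170 × [1/(1 − R²) − 1].

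| Assumed R² | Power | CI narrower by | Equivalent extra evaluable children (on 1170) |
|---|---|---|---|
| 0 | 82.1% | 0 | 0 |
| 0.01 | 82.5% | 0.5% | 12 |
| 0.02 | 82.9% | 1.0% | 24 |
| 0.05 | 84.1% | 2.5% | 62 |
| 0.10 | 86.1% | 5.1% | 130 |

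**Step 3: what R² might be plausible.** All prevalences and risk ratios in this step are assumed.
- District: for three equal districts, R² is the variance of the district prevalences divided by 0.15 × 0.85 = 0.1275. Prevalences of 12/15/18% give 0.005; 10/15/20% give [(0.05² + 0 + 0.05²)/3] / 0.1275 = 0.013; 5/15/25% give 0.052.
- One binary household factor present in 30–50% of children: a risk ratio of 2 gives about 0.02, and a risk ratio of 3 about 0.04–0.06.

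**Step 4: direction of the effect of ignoring district.** If stratification has removed a share R² from the true variance but the test uses the unreduced standard error, the actual two-sided error rate is about 2 × [1 − Φ(1.96/f)]. With R² = 0.013, f = 0.9935 and the rate is about 4.85%; with R² = 0.052, f = 0.9735 and it is about 4.4%. The crude test is therefore a little conservative, not anti-conservative. For the same reason the crude test's actual power is slightly above 82.1%, so for district alone the gains in Step 2 are, if anything, slightly generous.

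**The case against.** The case for leaving the plan alone is substantial. A crude prevalence ratio with a chi-square test is a valid analysis of a randomised comparison. It is the analysis on which the sample size rests, and it delivers the power claimed. The article gives no prognostic strength for any variable and does not list the household items, which are recorded 22 months before the primary endpoint. For an R² of 0.01 to 0.05 the gain is 0.4 to 2.0 power points. Ordinary variants of the same crude calculation differ by more: at 810 v 360 they run from 77.9% (log prevalence ratio, Wald) to 86.4% (unpooled). Adjusted analyses are also commonly left to an analysis plan, and that plan is not shown.

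Most of this stands and sets the weight of the point. It does not remove it. The article names a specific estimator and test rather than leaving them open, and that method omits the factor on which randomisation was stratified. Using the stratum is an improvement to what is written, not a request for missing detail. The objection bites hardest on the household variables, which cannot be named from the article; that is why district should lead.

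A reader might also infer more than the document supports:
- *The crude comparison is the only analysis planned.* The article says neither that it is the only one nor that adjustment is excluded.
- *Precision is certainly lost.* That would require an R² the document does not give.
- *Adjustment would remove chance imbalance in household exposure.* It would account only for imbalance in the variables included, and no imbalance is shown.
- *The gain is worth about 50, 130 or 280 children at R² of 0.02, 0.05 or 0.10.* Those figures scale all 2500 randomised children. Each comparison has 1170 evaluable children, which gives about 24, 62 or 130.

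**Conclusion.** The point holds as a minor, optional improvement. The stated primary analysis is valid and reaches its stated power, but it ignores the randomisation stratum, which tends to make it slightly conservative, and it makes no use of baseline data collected on every child. The likely benefit is small: 0.4 to 2.0 power points for an R² of 0.01 to 0.05, and 4.0 points at 0.10, which is more than any single binary factor in the working explains. District alone, with assumed prevalences of 10/15/20% (R² about 0.013), falls between the 0.01 and 0.02 rows, a gain of less than one point. These figures rest on the planning assumptions (15% v 9%, 810 v 360), on the (1 − R²) approximation, and on an R² that cannot be fixed from the document.

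**What to change.** Make the primary estimate for each schedule against control a district-adjusted marginal prevalence ratio with a 95% CI. Two routes are suitable:

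- a Mantel–Haenszel prevalence ratio and test stratified by district (if the ratio is the same in every district, this also equals the marginal ratio); or
- a logistic or modified-Poisson model with group and district, standardised to the trial population, with a robust CI.

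A few demographic or household variables from the enrolment form may be added on the model route, provided the list is fixed before laboratory results are linked to group. The Data management section places that linkage at the time of analysis. Keep the crude ratio and chi-square as a sensitivity analysis. If the analysis plan already specifies this, the sponsor need only confirm it.

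The cost is a few lines of text, a little more programming, a covariate list agreed in advance, and a simple rule for the occasional missing covariate value. No new data are needed, and the question (each schedule against control, as a marginal prevalence ratio) does not change.
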